### **6.1.1 Dosage**

The dose of GC1008 administered will be based on the patient's actual body weight (ABW) as measured on Day 0. Subsequent doses will be recalculated if the patient's weight changes by ≥10%.

## **6.2 Investigational Product**

GC1008 is an engineered human monoclonal antibody against human TGFβ1, β2, and β3

---

**6.2.1 Dose-Escalation Rules (Part 1)**

1. If 0 first-dose DLTs are observed out of 3 (or 4) patients treated with a dose-level, the next cohort of 3 (or 4) patients may be enrolled and treated at the next dose-level.
2. If 1 out of the 3 (or 4) patients treated with a dose-level experience a first-dose DLT, up to 3 additional patients (6 total) will be enrolled at that dose-level.
  - a. If only 1 out of these 6 patients experiences a first-dose DLT, then the next cohort of 3 (or 4) patients may be enrolled and treated at the next dose-level.
  - b. If  $\geq 2$  out of these 6 patients experience first-dose DLTs, then dose escalation is stopped. Additional patients will be enrolled at the prior lower dose-level to achieve a total of 6 patients.
3. If  $\geq 2$  out of 3 (or 4) patients in a cohort experience a first-dose DLT, dose escalation will be stopped. Additional patients will be enrolled at the prior lower dose-level, to achieve a total of 6 patients.
4. If 0 or 1 out of 3 (or 4) patients at the highest dose-level (15 mg/kg) experiences a DLT, additional patients will be enrolled to achieve a total of 6 patients.
  - a. If  $\leq 1$  out of these 6 patients experiences a DLT, the 15 mg/kg dose-level will be declared the maximal safe dose administered in this Phase 1 study.
  - b. If  $\geq 2$  patients experience a DLT, additional patients will be enrolled at the prior lower dose-level, for a total of 6 patients.

Escalation rules will be applied 28 days after the final patient in a given cohort receives the first treatment with GC1008. If  $\leq 1$  out of 6 patients at the highest dose-level (15 mg/kg) experiences a DLT, this dose-level will be declared the maximal safe dose used in this study.

If 15 mg/kg is not found to be safe, the MTD is defined as the next highest dose-level in which  $\leq 1$  out of 6 patients experiences a first-dose DLT.

**6.2.2 Guidelines for Treatment Delay, Dose Reduction, and Discontinuation (Part 2)**

Patients experiencing symptoms associated with skin events or AEs that in the opinion of the investigator require a treatment delay or dose modification should be discussed with the Sponsor. Treatment delays are allowed but if the time interval between planned doses is  $>56$  days (8 weeks), this will result in discontinuation of study treatment for the patient. (The only exception to this would be delays that are considered non-safety related or related to the evaluation of the event such as a delayed central pathology review).

---

### 6.2.2.1 Treatment Delays (Part 2 Only)

1. Treatment Delays
  - a. Treatment must be delayed after initial presentation of skin lesions until biopsies are obtained and the results are known. The type of biopsy performed is at the discretion of the site; however, it is recommended that a full thickness incisional or punch biopsy be performed to best evaluate these lesions. If multiple lesions occur, several lesions should be removed for purposes of sampling; the exact number of biopsies is at the discretion of the site. Treatment decisions may be made following site or local pathology review. All samples will be collected and reviewed by a central pathologist acting as consultant for Genzyme.
  - b. Treatment may be delayed at the Investigator's discretion if the patient is symptomatic
2. Re-treatment of patients whose therapy was delayed for symptoms
  - a. After a treatment delay with a minimum of 28 days (4 weeks) between planned doses, if symptoms improve, treatment may be restarted at the same dose at the Investigator's discretion. (Planned doses are administered at scheduled intervals of 2 or 4 weeks. If the interval between planned doses is 2 weeks, an additional 2 week delay is mandatory. If the interval between planned doses is 4 weeks, then no additional delay is required if symptoms improve.)

### 6.2.2.2 Dose Reduction (Part 2 Only)

In Part 2, all dose reductions should first be discussed between the Investigator and Sponsor. (No dose reductions were allowed in Part 1.)

If a patient in Part 2 develops worsening symptoms associated with skin events following re-treatment at the same dose level that are grade 3/4 (with the exception of new grade 3 skin cancers) or are intolerable, the dose may be dropped one dose level following a treatment break where symptoms improve to  $\leq$  grade 2 and become tolerable. For patients initially receiving GC1008 at 15 mg/kg, the dose will be reduced to 10 mg/kg, and for patients initially receiving GC1008 at 10 mg/kg, the dose will be reduced to 3 mg/kg. Only one dose level reduction is allowed per treatment course.

### 6.2.2.3 Discontinuation of Treatment Due to Skin Events (Part 2 Only)

All discontinuations should first be discussed between the Investigator and Sponsor prior to withdrawal of treatment. Treatment should be discontinued if:

- Patient experiences intolerable symptoms despite treatment of symptoms, treatment break and dose reduction,
-

- Patient develops multiple (>5) treatment emergent, skin cancers which are proven by biopsy and central pathology review to represent cancers that clearly do not have features representative of keratoacanthoma or “keratoacanthoma-like” SCC or melanoma
  - There is a significant change in risk/benefit, such as no evidence of reversibility following 8 weeks of observation off treatment
  - Use of systemic steroids or other prohibited medications is required to treat the skin lesions
-

## **7. EFFICACY AND SAFETY VARIABLES**

### **7.1 Efficacy and Safety Measurements Assessed and Study Flowchart**

The study will be conducted as outlined in the following sections, unless otherwise specified all assessments will be performed in both Parts 1 and 2 of the study. Study procedures and assessments are presented by visit for Parts 1 and 2 in Table 7-1 and for additional procedures conducted during Part 2 only in Table 7-2. At each visit, the site should confirm that patients with child-producing potential continue to practice effective contraception.

Response evaluations will be performed at 1 and 3 months following the planned 4 treatments. Whenever an objective response is noted, confirmatory scans or other appropriate studies must be obtained at least 4 weeks after the response is first documented. Study visits will be based on calendar days from Day 0.

---

**Table 7-1: Schedule of Study Events For Parts 1 and 2**

[illegible]

**Table 9-1: Schedule of Study Events For Parts 1 and 2 (continued)**

[illegible]

**Table 9-1: Schedule of Study Events For Parts 1 and 2 (continued)**

[illegible]

**Table 9-1: Schedule of Study Events For Parts 1 and 2 (continued)**

## Table footnotes:

-  Clinical laboratory tests include creatinine, calcium, phosphate, AST, ALT, total and direct bilirubin, LDH, alkaline phosphatase, BUN, sodium, potassium, chloride, bicarbonate, and complete blood count (CBC) with differential and platelets.
-  HIV testing must be performed within 3 months of patient consent.
-  Flu vaccine will be administered on Day -7 or earlier if the patient is enrolled during flu season.
-  PET CT scans alone may be used if normal resolution CT scans with contrast are performed as part of the study so that tumor measurements are accurate. Otherwise, normal resolution CT scans (with and without contrast) of the chest, abdomen, and pelvis must be performed in addition to the PET study.
-  If unavailable, platelet function tests (platelet aggregation [performed by standard or automated tests such as the PFA-100] and von Willebrand's factor) may substitute.
-  If the patient withdraws from the study, the patient must be followed for new AEs and SAEs for 45 days after the last dose.
-  These assessments are performed if the patient has not received alternative cancer treatment or has disease progression but has not declined recommended alternative cancer treatment.
-  PET CT scans are not required during Long-Term Follow-up.
-  Additional samples for anti-GC1008 antibody tests and PK may be requested during long-term follow-up if needed to complete the analyses.
-  If SAEs come to the attention of the site staff following the End-of-Treatment Visit, they will be reported to Genzyme if they may be causally related to study drug.

**Table 7-2: Schedule of Study Events For Additional Procedures Conducted During Part 2 Only**

|                                  | Screening and Baseline |              | Day 14 | Day 28 | Day 42 | Day 56 | Day 84 | Day 140
End-of-Treatment
Visit  |
|----------------------------------|------------------------|--------------|--------|--------|--------|--------|--------|---------------------------------------------------|
|                                  | Day -28 to -1          | Day -7 to -1 |        |        |        |        |        |                                                   |
| Skin Assessment      |                        | X            | X      | X      | X      | X      | X      | X                                                 |
| Complete Dermatologic Assessment | X                      |              |        |        |        |        |        |                                                   |
| Biopsy of uninvolved skin        | X                      |              |        |        |        |        | X      |                                                   |

 During Part 2, the physical examination will include a skin assessment.

 If the patient withdraws from the study, the patient must be followed for new AEs and SAEs for 45 days after the last dose.

**Table 7-3: Schedule of Study Events During Extended Treatment – Parts 1 and 2**

|                                                                                                                          | End-of-Initial Treatment  | Day 0 | Day 14 | Day 28 | Day 42 | Day 49                                 | Day 70  |
|--------------------------------------------------------------------------------------------------------------------------|---------------------------------------|-------|--------|--------|--------|----------------------------------------|---------------------|
| Physical Examination and Oral Assessment                                                                                 | X                                     | X     | X      | X      | X      | X                                      | X                   |
| Vital Signs                                                                                                              | X                                     | X     | X      | X      | X      | X                                      | X                   |
| Weight                                                                                                                   |                                       | X     | X      | X      | X      |                                        |                     |
| ECOG Performance Status                                                                                                  | X                                     | X     | X      | X      | X      | X                                      | X                   |
| Clinical Laboratory Tests                                                                                    | X                                     | X     | X      | X      | X      | X                                      | X                   |
| PT and PTT Tests                                                                                                         |                                       | X     |        |        |        |                                        |                     |
| Albumin and Magnesium                                                                                                    |                                       | X     |        |        |        |                                        |                     |
| Assessment of Tumor Measurement by Physical Examination                                                                  | X                                     | X     | X      | X      | X      | X                                      | X                   |
| CT Scan of Chest, Abdomen, and Pelvis; Assessment of Tumor Measurement by Radiographic and/or Other Methods  | X                                     |       |        |        |        |                                        | X                   |
| Blood GC1008 PK Assay                                                                                        | X                                     |       |        |        |        |                                        |                     |
| Blood GC1008 Antibody Assay                                                                                  | X                                     |       |        |        |        |                                        | X                   |
| GC1008 Infusion                                                                                                          |                                       | X     | X      | X      | X      | 6-week rest after 4 th dose |                     |
| SAE and AE Assessment                                                                                                    | X                                     | X     | X      | X      | X      | X                                      | X                   |
| Concomitant Medication/Therapy                                                                                           | X                                     | X     | X      | X      | X      | X                                      | X                   |
| Assess for Continuation of Extended Treatment                                                                            | X                                     |       |        |        |        | X                                      | X                   |

 The End-of-Initial Treatment Visit may be combined with another scheduled study visit, but evaluations must be completed within 35 days prior to Day 0 of Extended Treatment.

 Clinical laboratory tests include creatinine, calcium, phosphate, AST, ALT, total and direct bilirubin, CBC with differential, platelets, LDH, alkaline phosphatase, BUN, sodium, potassium, chloride, and bicarbonate.

 Restage the patient using CT or MRI scans (with and without contrast) of the chest, abdomen, and pelvis.

 After completing the final course of Extended Treatment, patients will undergo an assessment using the procedures outlined in the End-of-Treatment Visit; this visit will substitute for the Extended Treatment Day 70 visit. **For patients in Part 2**, additional PK and anti-GC1008 samples may be requested to complete analyses.

**Table 7-4: Schedule of Study Events During Extended Treatment – Part 2 Only**

|                              | End-of-Initial Treatment  | Day 0 | Day 14 | Day 28 | Day 42 | Day 49 | Day 70 |
|------------------------------|---------------------------------------|-------|--------|--------|--------|--------|--------|
| Skin Assessment  |                                       | X     | X      | X      | X      | X      | X      |
| Blood GC1008 PK Assay        |                                       | X     | X      | X      | X      | X      | X      |
| Blood GC1008 Antibody Assay  |                                       |       |        |        |        |        | X      |

 The End-of-Initial Treatment Visit may be combined with another scheduled study visit, but evaluations must be completed within 35 days prior to Day 0 of Extended Treatment.

 During Part 2, the physical examination will include a skin assessment.

## 7.2 Adverse Events

At each study visit, patients will be evaluated for new or evolving AEs. The physician should elicit symptoms using an open-ended question, followed by appropriate questions that clarify the patient's verbatim description of AEs or change in concomitant medications. A review of systems will be performed.

### 7.2.1 Part 1: Dose-Limiting Toxicity

A DLT is defined as any of the AEs defined below that occur within the first 28 days following the initial treatment with GC1008:

1. acute infusion reaction/cytokine release syndrome of  $\geq$  Grade 3 despite maximal appropriate therapy and allowing  $\geq 4$  hours for that therapy to take effect,
2. any hematological toxicity  $\geq$  Grade 3 that is considered causally related to GC1008, with the following exceptions:
  - a. Neutropenia will be considered dose-limiting only when the ANC is  $< 1,000/\text{mm}^3$  for  $> 96$  hours (4 days) or when it is associated with fever.
  - b. Thrombocytopenia will be considered dose-limiting only if platelets are  $< 50,000/\text{mm}^3$  for  $> 96$  hours (4 days), or
3. any  $\geq$  Grade 3 non-hematologic toxicity that is considered causally related to GC1008, with the following exceptions:
  - a.  $\geq$  Grade 3 diarrhea or vomiting will constitute a DLT only if it occurs despite treatment with optimal anti-diarrheals or anti-emetics.
  - b. If a patient with known liver metastases was enrolled with Grade 2 AST or ALT laboratory abnormalities at baseline, an increase in AST or ALT will be considered dose limiting only if the increase is  $> 3$  times the baseline and the elevation is confirmed  $\geq 5$  days later. (Note: the elevated values are Grade 3 by CTCAE criteria.)
  - c. If a patient with Gilbert's Disease was enrolled with a Grade 2 bilirubin abnormality at baseline, an increase in bilirubin will be considered dose limiting only if the increase is  $> 3$  times the baseline and the elevation is confirmed  $\geq 5$  days later.
  - d. Fatigue will be considered dose limiting only if  $\geq$  Grade 4.

There is no provision made in this protocol for reduction of the dose of the GC1008 treatment based on toxicity.

To expedite reporting, all DLTs will be collected using the SAE reporting mechanism.

Safety will be monitored and examined on a continuous basis and such reviews may lead to a modification of the treatment at any time.

### **7.2.2 Non-Tolerable Skin Events**

Non-tolerable skin events are defined as AEs that would not be expected to be ameliorated by dose, dose schedule modifications, or other treatments. These events may include:

- Skin lesions that involve >50% of the body surface, are symptomatic (pruritus, pain, etc.), and do not improve following appropriate symptom treatment, treatment break, and dose reduction
- The appearance of multiple (>5) treatment emergent skin cancers which are proven by biopsy and central pathology review to represent cancers that clearly do not have features representative of keratoacanthoma or “keratoacanthoma-like” SCC or melanoma.
- “Other” events that in the opinion of the investigator and the Sponsor are considered “non-tolerable” and unlikely to be ameliorated by schedule or dose modification

## **8. STATISTICAL METHODS AND PLANNED ANALYSES**

The Sponsor or designee will be responsible for:

- Patient listings
- Statistical analysis
- Combined clinical and statistical study report

All data recorded in eCRFs, as well as any outcomes derived from the data, will be presented in summary tables and/or data listings. The detailed analysis methods are included in the Statistical Analysis Plan.

In this study, patients may have more than 1 course of GC1008. A study report will be produced once all the patients in Parts 1 and 2 have either completed 1 course of GC1008 or discontinued from the study. An Addendum will follow upon completion of the study.

### **8.1 Demographics and Baseline Characteristics**

Demographic and other background variables will be summarized. For categorical variables, frequencies and percentages will be presented. Continuous variables will be summarized by mean, median, standard deviation, and range.

### **8.2 Concomitant Medication Usage**

Concomitant medication usage will be presented in individual patient listings.

### **8.3 Patient Accountability**

The number of patients who enrolled into the study, the frequency and percentage of patients who withdrew from the study, and the reasons for withdrawal, will be tabulated.

### **8.4 Study Treatment Usage and Compliance**

A summary of study treatment administration and compliance will be presented for all patients.

### **8.5 Efficacy Endpoints**

Tumor response (progressive disease, SD, PR, or CR) will be assessed by RECIST criteria, as discussed in Appendix B. Efficacy assessments will be made by the Investigator at the

investigational site. If necessary, Genzyme may request films and other components of response assessments for review.

Tumor response is being explored in this Phase 1 study. Patient data will be analyzed on the basis of tumor type and dose administered. The proportion of patients with CR; with PR or better; and with SD or better will be presented, along with the corresponding 90% confidence interval. The duration of responses will be examined, and progression-free survival will be estimated using the Kaplan-Meier method.

#### **8.5.1 Intent-to-Treat (ITT) Population**

The Intent-to-Treat (ITT) population includes all enrolled patients who are confirmed to be eligible for entry into the study and all treated patients, even if they are later determined to be ineligible. This set of patients will be referred to as the Full Analysis Set.

#### **8.5.2 Evaluable-for-Response Population**

The Evaluable-for-Response Population is a subset of the ITT population. Patients will be considered evaluable for purposes of assessing overall response rate and duration of response only if they have completed at least 1 treatment and have undergone at least 1 appropriate tumor response assessment. This set of patients will be referred to as the Per Protocol Set.

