Patients will be re-staged 1 month (Day 84) and 3 months (Day 140) following therapy. If the safety profile of this agent permits, patients who demonstrate evidence of SD or tumor response (CR or PR) by physical examination or radiographic study and/or improvement of symptoms by the time of the End-of-Treatment Visit may be offered Extended Treatment with GC1008 and receive up to 2 additional courses as long as the benefit is maintained.

Following completion of GC1008 treatment, patients will be asked to continue into long-term follow-up. Patients eligible for long-term follow-up include all patients who received GC1008 and meet criteria. Long-term follow-up visits will occur every 3 months for up to 2 years or until 1 of the criteria are met.

---

For all patients in Part 2, Patient Expansion, random biopsies of uninvolved skin will be obtained pre- and post-treatment with GC1008 for exploratory analyses. Any patient who develops treatment emergent skin lesions will undergo dermatologic evaluations. These evaluations may include skin biopsies and photo documentation. Samples of these biopsies will be made available for review by a central pathologist.

In order to assess the impact of this 4 dose regimen, patients in Part 2 may be replaced if fewer than 4 patients receive 4 doses of GC1008 and have not completed evaluations sufficient to assess safety. This decision will be made by the Sponsor in consultation with the DMC. However, patients experiencing skin changes who are unable to complete all doses because of the event would not be replaced, unless following a review of the case by the Sponsor in consultation with the DMC, it is determined that replacement of the patient is warranted.

Following completion of therapy of the final patient in the first cohort of patients *in Part 2, Patient Expansion*, all available safety data will be reviewed by Genzyme and the DMC to determine whether or not sufficient data have been obtained to meet the study's safety objectives and if continued enrollment is required. If it is determined that the safety objectives have not been met, a second cohort of 6 patients may be treated according to the same schedule described above. The decision whether to treat the second cohort of 6 patients at 15 mg/kg or to reduce the dose to 10 mg/kg would be based on the overall safety profile and the occurrence of "non-tolerable" skin events.

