### **8.12.2 Missing or Invalid Data**

Missing or invalid data will not be replaced.

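### Section 8.5.2 drops treated patients who never had a tumor assessment from the response-rate denominator, which biases the rate upward by a modest amount

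*Protocol*

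**What the plan says.** Section 8.5.2 defines the Evaluable-for-Response Population as a subset of the ITT population and ties it to two endpoints, the overall response rate and how long responses last. For these, a patient counts "only if they have completed at least 1 treatment and have undergone at least 1 appropriate tumor response assessment". The section then adds a label: "This set of patients will be referred to as the Per Protocol Set".

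Section 8.5.1 defines a wider set, the ITT or Full Analysis Set. It takes in eligible enrolled patients and also "all treated patients, even if they are later determined to be ineligible". The protocol does not say which efficacy results use it.

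Section 8.5 lists the results to be reported: "The proportion of patients with CR; with PR or better; and with SD or better will be presented", each with a 90% confidence interval and analysed by tumor type and dose. It names no population.

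On timing, Section 7.1 says: "Response evaluations will be performed at 1 and 3 months following the planned 4 treatments". For Part 2, Section 4.1.2 says: "Patients will be re-staged 1 month (Day 84) and 3 months (Day 140) following therapy".

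For early withdrawals, Section 5.3 asks the investigator to make every effort to carry out the End-of-Treatment procedures within 30 days. Under Table 5-1 the restaging CT or MRI is skipped only if one was done in the 30 days before that visit. Section 8.12.2 says: "Missing or invalid data will not be replaced".

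**The concern.** Whether a patient has a response assessment depends partly on how the patient fares. Those treated here have inoperable or metastatic disease, have failed at least one prior therapy, and may have ECOG status up to 2. A treated patient who dies, or becomes too ill to be scanned, before any assessment has failed treatment. Under Section 8.5.2 that patient is not a non-responder but is absent from the calculation. Membership of the denominator then depends on the outcome being measured.

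At stake is the estimate for a secondary objective in both parts, the preliminary look at clinical activity, which is to be reported with confidence intervals. If the SD-or-better proportion uses the same set it moves the same way, because an unassessed patient has no documented stable disease either.

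**Working it through.** **1. When assessments fall due.** The first dose is on Day 0. A 28-day observation period follows, then three doses 14 days apart, on Days 28, 42 and 56. One month after the last dose is 56 + 28 = Day 84, and three months after is 56 + 84 = Day 140, as Section 4.1.2 states. Planned response evaluation thus starts 12 weeks after first treatment.

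**2. Which set governs the rate.** Section 8.5.2 names overall response rate and uses the words only if. Section 8.5.1 names no endpoint, and neither does the reporting sentence in Section 8.5. Section 8.5.2 is the only text that links a response rate to a population.

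**3. The plan's own figures.** Section 8.11 gives lower 90% limits of 5.9%, 8.6% and 11.5% for 4, 5 and 6 responders in 24. The exact (Clopper-Pearson) lower limit for x responders in n is the 5% quantile of a Beta(x, n − x + 1) distribution. At n = 24 it gives 5.90%, 8.59% and 11.49%, so the stated figures reproduce. The same method is used below.

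**4. Effect of the exclusion.** Let N be the number treated, x the responders and k the treated patients never assessed.

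- All treated: rate = x / N.
- Section 8.5.2: rate = x / (N − k).
- Ratio of the second to the first: N / (N − k), which is above 1 whenever k > 0 and x > 0.

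Take N = 28, from 22 treated in Part 1 plus 6 in the first Part 2 cohort (Section 4.1.2), and x = 4 as an illustration. The protocol gives no value for k, so a range is shown.

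| k (assumed) | Rate | Exact 90% CI |
|---|---|---|
| 0 | 4/28 = 14.3% | 5.0% to 29.8% |
| 1 | 4/27 = 14.8% | 5.2% to 30.8% |
| 2 | 4/26 = 15.4% | 5.4% to 31.8% |
| 4 | 4/24 = 16.7% | 5.9% to 34.2% |
| 8 | 4/20 = 20.0% | 7.1% to 40.1% |

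The rise is 0.5 points at k = 1, 1.1 at k = 2, 2.4 at k = 4 and 5.7 at k = 8.

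**5. The plan's own sample size.** With N = 24 and x = 5, the rate is 5/24 = 20.8% (lower limit 8.6%). It becomes 5/23 = 21.7% (9.0%) at k = 1, 5/22 = 22.7% (9.4%) at k = 2, 5/20 = 25.0% (10.4%) at k = 4 and 5/18 = 27.8% (11.6%) at k = 6.

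**6. Small groups.** Section 8.5 analyses by tumor type and dose. In a cohort of 6 with 1 responder, the rate is 1/6 = 16.7%. One unassessed patient makes it 1/5 = 20.0%, and two make it 1/4 = 25.0%.

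**The case against.** The strongest reply is that two efficacy sets are defined, that a Full Analysis Set with no use would be odd, and that the SAP, which is not at hand, may report response in both. Part of this stands. The SAP may add an all-treated analysis, and Section 8.5 leaves the set for its three proportions open. But Section 8.5.2 is a stated restriction on overall response rate, not a silence for the SAP to fill.

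The second reply is that few patients would be lost. Entry requires an expected survival of at least 5 months and serum albumin of at least 3.0 g/dL. Withdrawn patients are to be restaged, and most who stop early enter three-monthly follow-up. The main visit table (Table 7-1) cannot be read in the copy at hand, so a qualifying tumor assessment before Day 84, for example by physical examination, cannot be excluded. All of this stands. It makes k smaller but not zero.

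Some stronger readings are tempting but unsupported:

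- A reader might infer that every patient who deteriorates before Day 84 is lost. The restaging at withdrawal keeps many of them in; only those who die first or are never assessed drop out.
- A reader might take Section 8.12.2 as confirming the exclusion. It bars replacing missing values. Counting an unassessed patient as having no documented response replaces nothing.
- A reader might infer that duration of response is inflated too. It is not, since an unassessed patient cannot be a documented responder and would add no duration.
- A reader might infer that the rate sets the assumptions for the later Phase 2 melanoma study. Section 4.1.2 says Part 2 helps define dose levels, schedule and dose modification guidelines. It does not mention a response-rate assumption.

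**Conclusion.** The point holds for overall response rate. As written, Section 8.5.2 removes treated patients who are never assessed, and the bias can only be upward. For SD-or-better the same follows only if that proportion uses the evaluable set, which the protocol does not say.

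The size depends on an unknown number of unassessed patients. With 1 or 2 of 28 the shift is about half a point to one point. It reaches 5.7 points only if 8 of 28 are unassessed, and even then the two intervals overlap widely. In a cohort of 6, one or two unassessed patients move the rate by 3.3 or 8.3 points.

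The consequence is modest. Response is a secondary, exploratory endpoint with no test or decision rule attached, and Section 8.11 itself expects little from the response statistics. The change is still worth making because it is cheap and removes a bias of known direction.

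**What to change.** In Sections 8.5 and 8.5.2, state that the CR, PR-or-better and SD-or-better proportions and their 90% confidence intervals use all treated patients as the denominator. Add that a treated patient with no post-treatment tumor assessment counts as a non-responder and as not SD. Keep the Evaluable-for-Response Population as a labelled sensitivity analysis, and report the number of treated patients it leaves out.

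This changes wording only and needs no new patients, visits or data. The cost is that the reported rates will be slightly less favourable.
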